#### Exclusion criteria:

- Lack of the above criteria

### 5.3 Recruiting

Recruitment of research participants will be performed using the process already adopted for the metabolic newborn screening programs in participating countries. In Italy, this includes 48 rare diseases and is well established in all Regions, although with some differences. Following the already existing NBS pipeline will ensure to address and recruit a representative sample without neglecting any minority meeting the concepts of equality and equity also in relation to the well-known heterogenous ethnic

composition of European population due to the important immigration phenomenon which is ongoing in all Member States.

The recruitment will be competitive and will last at least 12 months (with the possibility of extension to reach the enrolment target).

In detail, the information to the parents will be carried out through dedicated videos, flyers/leaflets, and meetings during one or more pregnancy checkpoints (CKPTs): an early CKPT in the first half of pregnancy, a major checkpoint at the end of pregnancy and a rescue checkpoint just after birth at DBS collection for biochemical NBS.

The administration of dedicated videos at the various CKPTs will take place always in the presence of healthcare personnel (gynaecologist/midwife/neonatologist/geneticist). The dedicated videos will also be available online -S4C website (<https://screen4care.eu/>)- should the couple wish to review them later; moreover, it will be possible to make requests for further clarification since the dedicated project' email address [[contact]](mailto:[contact]) is available. Furthermore, on the S4C website will be published a poster describing the procedure and a section dedicated to FAQs ("*Frequently asked questions*") is also planned.

If parents give consent to project' participation, a project dedicated DBS card reporting the S4C logo (S4C-DBS) will distributed at S4C birth centers to collect blood samples from enrolled neonates and then shipped to the S4C sequencing Hub (OPBG, Rome Italy) where all European samples, will be sequenced.

**Important Note:**

The couples' choice to participate to the two different cohorts' studies (TREAT-panel and TREAT-WGS) will be free, recruitment will be competitive in both cohorts, meaning that when reached the established number of infants to be screened (200 for TREAT-WGS, and 18.000 for the TREAT panel) the recruitment will be closed for both cohorts.

A schematic representation of gNBS pipeline is reported in **Appendix IV**.

## 6 Methods and realisation

### 6.1 Sample collection and analysis

Samples will be collected on the dedicated S4C DBS card in parallel with the collection of the DBS card of the metabolic newborn screening. Then samples will be pseudonymized at S4C birth centres and shipped to OPBG Hub, for DNA extraction and TREAT-panel NGS sequencing.

For a list of genes screened by panel for TREATable diseases see **Appendix V**.

Extracted DNA from S4C DBS cards will be conserved as pseudonymized at the OPBG hospital for the entire S4C duration, as described in Deliverables. OPBG will be responsible partner for sample conservation. If specified and agreed in the informed consent, S4C DNAs can be used for research purpose only for future S4C activities only, in their strictly anonymized habit. In some (expected a few) cases of cohort TREAT-WGS, when DNA quality extracted from the DBS might not be adequate, a

newborn peripheral blood sample taken might be needed and requested to the couple, as clearly mentioned in the informed consent.

The OPBG Hub will transmit by a dedicated, encrypted cloud platform BaseSpace (the S4C data repository, described in WP2) the raw data of gNBS sequencing output. Data will be therefore analyzed by two different partners: CNAG (Centro Nacional de Analisis Genomico) in Barcelona and Genoox in Tel Aviv, which will have access to this platform and are fully committed to be adherent to the ethical and confidentiality rules of S4C, as described in Deliverable D6.11 ([document attached](#)).

Results will be available to consortium members and through the RD-Connect GPAP and Genoox/CNAG platforms (whose access is limited to S4C consortium partners only and double-checked). These will make the data FAIR-field and sharable within the project in a privacy-preserving and controlled data access environment. As the aim of the TREAT-panel is to identify diseases where early diagnosis and treatment might benefit the health of the affected infant, the scientific report (prepared and finalized by CNAG and GENOOX) will report all variants identified in the TREAT genes. This report will be delivered to S4C validation Hubs (OPBG, UNIFE and Freiburg) that will perform variants' evaluation ("manual curation") and eventually a technical validation of the identified variants.

In all newborns (both cohorts) in which the "manual curation" of the scientific report (i.e. variants' evaluation) and the eventual technical validation will confirm the pathological genotype, the couples will be contacted by birth centers who will direct them to the closest (disease specificity and logistical point of view) competent ERNs.

In detail, to be compliant with the Consortium Agreement rules, the birth centers will provide the family with a written curated scientific report (a document intended exclusively for research purposes) including the closer and competent ERN address and contacts.

The ERN centre will provide a diagnostic grade report (requiring a diagnostic confirmation performed on a new sample from the newborn and on the parents). The diagnostic report will include only the following genetic findings:

- Pathogenic or likely pathogenic variants in appropriate inheritance model and according to penetrance characteristics

VUS will not be validated nor reported in the scientific and in the diagnostic report. In case of identification of a VUS, a pipeline to further study *in silico* or by functional studies of the VUS will be established at the ERN clinical and diagnostic centres as part of the research flow also (if feasible) via collaboration with the European Joint Programme ERDERA ([Preparing the path to the European Rare Diseases Research Alliance](#)) which will be dedicated to VUS collection and analysis. As already mentioned above, only TREAT panel-related genes variants will be called and reported.

Summarizing, a scientific report will be generated by CNAG/GENOOX, and this will come back to S4C Hub (OPBG, UNIFE, and Freiburg) that will provide "manual curation" (i.e. variants' evaluation) and eventually technical validation of the identified variants.

The birth centers will provide the family with a written curated scientific report (a document intended exclusively for research purposes) including the closer and competent ERN address and contacts.

The ERN centre will be in charge to provide a diagnostic grade report, which requires a diagnostic confirmation performed on a new sample from the newborn and on the parents.

We estimate that more than >95% of study participants will not carry any of the above-mentioned pathogenic or likely pathogenic variants as for rare or ultrarare diseases included in the TREAT panel.

The gNBS (through TREAT-panel and TREAT-panel in silico with WGS backbone ) may therefore have three results:

- a negative result: in this case the family will receive a written information (via “PEC” mail or by digital tools, including electronic health records –EHRs- or -subject to the approval of the DPO- “*fascicolo sanitario*” in Italy) stating that the S4C did not identify any variant in the TREAT disease genes
- result with variants of unknown significance: in a case of an identification of a VUS, a pipeline to further study *in silico* or by functional studies of the VUS will be established at the ERN clinical and diagnostic centre (if applicable through the ERDERA project). No result will necessarily have to be communicated to the couple.
- a positive result: in this case the family will be contacted by the Birth Center which will provide a written curated scientific report and then will address the couple and baby to ERNs for a multidisciplinary post-test counselling for diagnosis communication, explanation of clinical and reproductive implications, access to available therapies and clinical and instrumental follow-up
- Carrier status for recessive pathogenic variant will be reported only if agreed on the informed consent, and provided on separate form. Since positive babies data analysis and communication is a priority of S4C, carrier status will be eventually communicated as a secondary endpoint and only in Italy, at the end of the project, and when all positive cases would have been solved and correctly addressed to ERNs.

As above mentioned after completion of the study all data will be stored at the S4C repository (WP2) and can be used for additional research purposes only and fully anonymized. To do so, the results will only be reported as aggregated data to avoid potential re-identification of study participants.

Regarding the estimation of critical cases identifiable through TREAT-panel, if we consider the number of total newborns enrolled in S4C study (approximately 18.000 for the cohort TREAT-panel and 200 for the cohort TREAT-WGS), we therefore expect to identify approximately 500 newborns in Europe (Italy, France, Germany, Czech Republic, Greece, Poland), approximately 250 newborns in Italy and approximately 125 newborns in Emilia-Romagna.

**Appendix VI** shows a Figure with estimation of critical cases identifiable by TREAT-panel based on the frequency of rare, very rare and ultrarare diseases (as per Eurordis study, Reference reported in the Figure).

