## 4 Study goals

### Primary endpoints:

- Percentage of eligible couples who will accept to participate to the TREAT-panel (Cohort TREAT panel)
- Percentage of eligible couples who will accept to participate to the TREAT-panel in silico with WGS backbone (Cohort TREAT-WGS)
- Percentage of study participants in whom a pathogenic or likely pathogenic variant in appropriate inheritance model will be identified through TREAT-panel
- Percentage of study participants in whom a pathogenic or likely pathogenic variant in appropriate inheritance model will be identified through TREAT- WGS
- Percentage of study participants resulted fully negative at the gNBS (through both TREAT-panel and TREAT- WGS)

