## 6.2 Follow-up for study participants

### Participants with no pathogenic or likely pathogenic variant

Negative result (expected to be about >95% of screened infants) will be communicated to the couple by written information (via “PEC” mail or by digital tools, including electronic health records –EHRs- or - subject to the approval of the DPO- “*fascicolo sanitario*” in Italy) stating that the S4C did not identify any variant in the TREAT disease genes. If participants should develop symptoms suggestive of a genetic disease within 12-24 months of life, whole genome sequencing of the entire Mendeliome will be offered for further clarification (not described here, since part of the separate specific ethical application).

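### The negative letter says no variant was found, but the >95% expected to receive it is defined so that it includes recessive carriers

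*Protocol*

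**What the plan says.** Section 6.1 limits the diagnostic report to "Pathogenic or likely pathogenic variants in appropriate inheritance model and according to penetrance characteristics". It then estimates that "more than >95% of study participants will not carry any of the above-mentioned pathogenic or likely pathogenic variants". The estimate refers back to that list, so it counts infants without a disease-causing genotype.

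Section 6.1 next announces three results: negative, VUS and positive. Negative families receive written information "stating that the S4C did not identify any variant in the TREAT disease genes". For a VUS, "No result will necessarily have to be communicated to the couple". A further bullet covers carriers, who are told on a separate form if the consent allows; it adds that "carrier status will be eventually communicated as a secondary endpoint and only in Italy, at the end of the project". The expected yield is "approximately 500 newborns in Europe", from about 18,000 panel and 200 TREAT-WGS infants.

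Section 6.2 attaches the same percentage to the letter: "Negative result (expected to be about >95% of screened infants") is communicated in writing, with the same statement about variants.

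Section 4 has a primary endpoint, "Percentage of study participants resulted fully negative at the gNBS", without saying whether carriers or VUS infants count. Carrier frequency and the VUS percentage are secondary endpoints. Sections 1 and 7.2 describe carrier return on request or by consent, without the limit to Italy and to project end.

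**The concern.** Two meanings of negative are in use. The letter's meaning is that nothing was found in the TREAT genes. The meaning behind the >95% is that no disease-causing genotype was found. A carrier of a single recessive allele satisfies the second and not the first, and the study expects to find carriers, because it counts them.

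At stake is a written statement to parents, possibly placed in a health record, on a matter with reproductive consequences. In Italy, couples who consented would later receive a carrier form contradicting their letter. Elsewhere nothing would correct it. The primary endpoint on fully negative infants is exposed to the same ambiguity.

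**Working it through.** **Step 1: reproduce the >95%.** Inputs from section 6.1: 500 expected positives and 18,000 + 200 = 18,200 infants.

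- Positive: 500 / 18,200 = 2.75%.
- Not positive: 100% − 2.75% = 97.25%, or 17,700 infants.

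The >95% is therefore reproduced as the complement of the positives, with carriers and VUS infants counted inside it.

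**Step 2: ask whether >95% could also hold on the letter's meaning.** Carriers and VUS infants together would have to fit into 5% − 2.75% = 2.25 points.

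Under Hardy-Weinberg, a recessive condition with frequency p has allele frequency q = √p and carrier frequency 2q(1 − q). At 1 in 10,000, the low end of the rare class in section 10.6, q = 0.01:

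- One such condition: 2 × 0.01 × 0.99 = 1.98% carriers.
- Two: 1 − 0.9802² = 3.9%, above the 2.25 points available.
- Three: 1 − 0.9802³ = 5.8%, above 5% even if there were no positives at all.

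**Step 3: illustrate the size.** The protocol does not say how many panel conditions are autosomal recessive, so this share, f, is an assumption. Section 10.6 is read as 40 rare, 100 very rare and 100 ultrarare conditions. Each is set at the lowest frequency in its class (carrier frequencies 1.98%, 0.63% and 0.20%), with one gene per condition.

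Share carrying at least one allele = 1 − 0.9802^(40f) × 0.9937^(100f) × 0.9980^(100f). Share with no finding on the letter's meaning = 97.25% × (1 − carrier share), before VUS infants are removed.

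| Assumed recessive share | Carriers | No finding, letter's meaning | Non-positive carriers (of 17,700) |
|---|---|---|---|
| 5% | 7.8% | 89.6% | about 1,390 |
| 10% | 15.1% | 82.6% | about 2,670 |
| 25% | 33.5% | 64.7% | about 5,930 |
| 50% | 55.8% | 43.0% | about 9,880 |

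Two checks on the low side. With only 1% of conditions recessive, carriers are 1.6% and would fit in the 2.25 points if there were almost no VUS infants. With 2.5% (6 of 240 conditions), they are 4.0% and do not fit. If all 240 conditions were ultrarare and half recessive, carriers would still be 21%.

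**The case against.** The strongest reply is that no sentence says carriers receive the negative letter. They have their own bullet in section 6.1, and the section 6.2 subheading on participants without a pathogenic or likely pathogenic variant would, read literally, leave them out. This stands as a fact about the text. It does not rescue the plan: with carriers left out, they have no result path, and the >95% meets the difficulty in step 2.

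A second reply is that the letter's statement is shorthand for a reportable variant. Section 6.1 has the scientific report list every variant in the TREAT genes, so a strictly literal letter would be untrue for more than carriers. The template and consent pages are not available and may carry a caveat. That reading is possible, but sections 6.1 and 6.2 both specify the statement without qualification, and section 6.1 separates VUS from negative, so the shorthand is not applied consistently.

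Three stronger readings are not supported:

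- A reader might infer that thousands of untrue letters are established. The counts in step 3 rest on an assumed recessive share and are upper limits under each assumption, because a carrier who also has a VUS may get no letter.
- A reader might infer that the primary endpoint has two stated values. The protocol prints none, and finer classification may sit in an analysis plan that is not shown. What the protocol does contain is a term whose strict sense conflicts with its own >95%.
- A reader might infer from the sparse record in section 9.7 that carriers could not be separated later. The same section keeps the panel and TREAT-WGS data for the project's duration, so their status stays recoverable.

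**Conclusion.** The point holds as a conflict in the current text. The group expected to receive the letter is defined by inheritance model, and the letter then makes a broader claim that is untrue for any carrier counted as negative. The alternative, that carriers are not negative, leaves them without a result class and makes >95% implausible.

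The contradiction needs no carrier estimate, since one carrier is enough. The implausibility of >95% on the strict meaning needs only the protocol's 2.75% expected positives, Hardy-Weinberg, and two recessive conditions at 1 in 10,000. The wider range, 7.8% to 55.8% carriers, shows direction only. The same looseness affects VUS infants, who are inside the >95% but form a separate result in section 6.1. The correction is worth making before further letters are sent, because letters cannot readily be recalled.

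**What to change.** - **Letter (6.1 and 6.2).** Replace the statement with: *no pathogenic or likely pathogenic disease-causing genotype was identified in the TREAT genes; this letter does not report carrier status or variants of uncertain significance*. State that carriers receive this letter. Leave section 6.1's rule on telling VUS families as it is, unless the sponsor chooses to change it.
- **Primary endpoint (4).** Say whether fully negative includes carriers and VUS infants. If it includes both, it is simply the complement of the positive-yield endpoints, and the sponsor should choose with that in mind.
- **The >95%.** Attach it only to the absence of a pathogenic or likely pathogenic variant in the appropriate inheritance model. Report the percentage with no pathogenic, likely pathogenic or VUS allele as a separate figure.
- **Carrier return (1 and 7.2).** Add the limit to Italy and to project end that section 6.1 already sets.

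The cost is one letter template, one endpoint definition and wording in sections 1, 4, 6.1, 6.2 and 7.2, with no extra samples or sequencing. The letter becomes slightly less reassuring, and birth centres should expect more questions about carrier status.

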## 6.2 Follow-up for study participants

### Participants with no pathogenic or likely pathogenic variant

Negative result (expected to be about >95% of screened infants) will be communicated to the couple by written information (via “PEC” mail or by digital tools, including electronic health records –EHRs- or - subject to the approval of the DPO- “*fascicolo sanitario*” in Italy) stating that the S4C did not identify any variant in the TREAT disease genes. If participants should develop symptoms suggestive of a genetic disease within 12-24 months of life, whole genome sequencing of the entire Mendeliome will be offered for further clarification (not described here, since part of the separate specific ethical application).

### Participants with pathogenic or likely pathogenic variants

As anticipated S4C validation Hubs (OPBG, UNIFE, and Freiburg) will provide “manual curation” (i.e. variants’ evaluation) and eventually technical validation of the identified pathogenic/likely pathogenic variants with appropriate inheritance model and according to penetrance characteristics. If validated, the birth centers will provide the family with a written curated scientific report (a document intended exclusively for research purposes) including the closer and competent ERN address and contacts. All S4C partners involved in gNBS are members of many ERNs (see the list in the **Appendix III**) therefore the path to address positive infants to excellence diagnostic centers will be timely and smoothly planned. All phenomic categories associated with disease-genes included in TREAT-panel will be therefore followed up by the relevant reference ERN (**Appendix VII**).

## 7 Assessment of benefits and risks

### 7.1 Benefits of participation

Study participants might benefit from early diagnosis of a rare genetic disease and consequent timely access to treatments, as per the definition of the TREAT-panel, where genes were primarily scored for the availability of treatments in the corresponding rare diseases.

The criteria of treatability implies “Approved drug treatment (EMA) that includes gene therapy and/or other treatment/intervention (drug, diet, bone marrow transplantation, supplements, vitamins etc) that is recommended by guidelines (at least for a subgroup of the disease) and treatment available in Italy” (see **Appendix II**).

It is well known that benefit might be greater if treatment is initiated in the pre-symptomatic or early stage of the disease. Early diagnosis of a rare disease might also reduce the burden of multiple diagnostic tests and periods of uncertainty that are often associated with the “diagnostic odyssey” of a rare disease. Study participants with no abnormalities might benefit from the reassurance that presence of any of the rare diseases screened is very unlikely (accuracy grade 97%).

Regarding the application of WGS as a “technical validation tool” of the TREAT-panel, this approach can result in a number of benefits.

Indeed, since exclusively the genes included in the TREAT-panel will be interrogated, this innovative approach minimises the amount of data generated and the presence of VUS and lacks the risk of communicating “incidental findings” or “secondary findings”; moreover, it offers the great potential to technically validate the TREAT panel output especially from some variant types as copy number and structural variants. The eventually stored genomic data might be reconsidered for further research use, pending the signing of the informed consent.

## 7.2 Risks of participation

The blood samples for the genetic newborn screening are taken in parallel with the national metabolic newborn screening (both on DBS cards). Thus, there are some procedure-related risks, i.e. flushing or pain for the participating infant and a small risk of infection, but the midwife will wear gloves and clean the heel of the babies before collecting the blood to reduce the risk as far as possible. Regarding the genetic analysis carried out, it is possible that the test performed results negative because of the limitation of the technique used (for this reason, the quality parameters of the analysis are indicated in the report). In addition, parts of some genes may have characteristics that make their analysis problematic: such parts may be partially excluded from the results because they are difficult to evaluate by sequencing techniques. In light of this, the sub-study based on WGS as a technical validation tool, is planned to compare the feasibility, detection rate and gene coverage of the two methods (TREAT-panel vs TREAT-panel in silico with WGS backbone) thus conferring robustness to the TREAT panel diagnostic grade..

Finally, the gNBS may also identify carriers of recessive (both autosomal and X-linked) diseases, although this is not the goal of the gNBS protocol. Carrier status might be communicated if agreed in the informed consent (only upon request by legitimate subjects, i.e., parents or legal tutors).

